## Discussion

As stated above, wrist trauma is frequently encountered at the Emergency Department. However, to this date, no decision rule regarding this type of trauma has been created.

Ideally, we would like to obtain radiographs of every patient entering one of the participating hospitals with trauma to the wrist. This however, is ethically and logistically not feasible. Therefore we should acquiesce to the fact that we obtain the informative parameters listed on the Case Report Form of each patient presenting with wrist pain post injury, but only outcome data on patients sent for X-ray by their treating physician. Any comments on this approach can be invalidated by stating that patients, for whom no radiography is required according to their physician, are not suspected of having a distal radius fracture and thus are not part of our domain.

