### Study population

The study population is defined as all consecutive adult patients presenting at the Emergency Departments in the participating hospitals following wrist trauma and who are suspected to have sustained a distal radius fracture. Patients are suspected of having sustained a distal radius fracture when pain on pressure in the wrist area is indicated. The wrist is defined as the proximal segment of the hand consisting of the carpal bones and the associated soft parts and the distal segment of the ulnar and radial bone. A traumatic wrist injury is defined as a high or low energetic accident involving the wrist, e.g. a fall on the outstretched hand or a motor vehicle accident.

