#### Inclusion criteria

• Patient aged 18 years and older

• An acute trauma of the wrist (< 72 hrs following trauma)

• Pain on pressure in wrist area

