#### Exclusion criteria

• Pre-existent neurological pathology in the affected limb

• Previous fracture of distal radius <3 months

• Patients referred from another hospital where X-rays of the wrist were performed

• Multi trauma patient

• Patients who are not considered to be competent or capable by their treating physician to answer any questions regarding pain or mechanism of trauma as listed on the Case Report Form (Additional file 1).

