### Statistical analysis

The data from the academic hospital and the non-academic teaching hospital will be used to develop the model. The data will be assessed by using a multivariable analysis. However, to prevent too optimistic estimates of the accuracy of the diagnostic model, a more liberal p-value for statistical significance will be employed (p = 0.15). Logistic regression modeling will be used to estimate the regression coefficients and thus the log odds of a fracture versus no fracture after which a reduced model will be created by means of a log likelihood ratio test.

The accuracy of the model will be estimated by a goodness of fit test and a ROC curve. If applicable, different models can be compared using the tests mentioned above. The final model will be validated internally through bootstrapping to estimate overfitting in the calibration and discrimination stated above. By averaging the optimism an adjusted model will be generated.

Henceforth, the prediction rule will be validated in a new data set, which will be collected simultaneously in the third hospital; the non-teaching hospital. If necessary, the model will be updated using the data from the validation study, by adjusting the intercept.

Finally, the prediction model will be presented as a simplified risk score which can be used by physicians to determine the need for an X-ray in patients presenting with wrist trauma at the Emergency Department.

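### The Discussion places patients who are not X-rayed outside the domain, against the protocol's own definition of the study population, so the rule's performance will describe imaged patients only

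*Protocol article*

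**What the plan says.** For distal radius fractures, Study population takes in "all consecutive adult patients presenting at the Emergency Departments in the participating hospitals following wrist trauma and who are suspected to have sustained" one, and then defines suspicion in operational terms: "Patients are suspected of having sustained a distal radius fracture when pain on pressure in the wrist area is indicated". Inclusion criteria repeats this as "Pain on pressure in wrist area". The only exclusion that mentions imaging is "Patients referred from another hospital where X-rays of the wrist were performed". No criterion requires an X-ray at the study hospital or excludes patients who do not get one.

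On data collection, the Discussion says that predictors are recorded for everyone: "we obtain the informative parameters listed on the Case Report Form of each patient presenting with wrist pain post injury". For the outcome its statement is narrower: "but only outcome data on patients sent for X-ray by their treating physician". It then argues that "patients, for whom no radiography is required according to their physician, are not suspected of having a distal radius fracture", places them outside the domain, and presents this as an answer that defeats any comment on the approach. The abstract's Discussion paragraph makes the same argument more cautiously, as something that could be argued.

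The primary aim in Background is to decide when an X-ray is necessary in patients who come to the Emergency Department after wrist trauma. Statistical analysis ends with a risk score that "can be used by physicians to determine the need for an X-ray in patients presenting with wrist trauma at the Emergency Department".

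**The concern.** A patient with acute trauma and pain on pressure who is not X-rayed is suspected and eligible under Study population and Inclusion criteria, but not suspected and outside the domain under the Discussion. Both cannot hold.

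The Discussion's version is also circular. The rule is meant to inform the decision to X-ray, yet that decision, as taken without the rule, defines the population in which the rule is built and tested.

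This is partial verification. The X-ray reading is the only outcome source named (Main study parameter/endpoint). According to Study procedures the treating physician completes the Case Report Form (CRF), and according to the Discussion the same physician decides on imaging. Whether the outcome is known will therefore plausibly depend on the candidate predictors. The third hospital collects data in the same way, so external validation would not reveal the problem. Fracture prevalence among imaged patients also reflects local imaging habits, so an updated intercept could partly absorb those habits.

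For a rule that withholds X-rays, the figure that matters most is the share of fractures missed in the patients to whom it will be applied. X-rays that the rule would newly trigger in patients who are not imaged today cannot be seen in the planned data.

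**Working it through.** **The plan's own figure.** Sample size asks for 10 events per parameter: 20 × 10 = 200 fractures. With 500 patients and about 50% fractures, 500 × 0.50 = 250, which covers 200. The figure reproduces and is not in dispute. The 50% is a share of radiographs, so it describes imaged patients only.

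**The definitions side by side**, for a patient with acute wrist trauma, pain on pressure and no X-ray:

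| Section | Suspected? | In the population? |
|---|---|---|
| Study population, Inclusion criteria | yes | yes |
| Exclusion criteria | – | not excluded |
| Discussion (and, more softly, the abstract) | no | no |

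The contradiction needs no assumed number.

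**What it could do to performance.** The protocol gives neither the share of eligible patients not imaged nor their fracture rate, so the following inputs are assumptions except the 50%. Among imaged patients: 50% fractured, apparent sensitivity 98%, apparent specificity 30%. Among eligible patients: 20% not imaged, 3% of these fractured, 90% of these rule-negative whether fractured or not. Per 1,000 eligible patients:

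- Imaged: 800, of whom 400 have a fracture (392 detected, 8 missed) and 400 do not (120 rule-negative, 280 rule-positive).
- Not imaged: 200, of whom 6 have a fracture (6 × 0.9 = 5.4 missed) and 194 do not (194 × 0.9 = 174.6 rule-negative).
- Sensitivity = 1 − (8 + 5.4)/406 = 96.7%, against 98% apparent.
- Specificity = (120 + 174.6)/594 = 49.6%, against 30% apparent.
- X-rays under the rule = 392 + 280 + 200 × 0.1 = 692, against 800 now: a reduction of 13.5%. In imaged patients alone, 1 − 672/800 = 16%.

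Extremes of sensitivity over 10–20% not imaged, 2–5% of these fractured and 80–90% rule-negative:

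- Lowest (20%, 5%, 90%): (392 + 1)/410 = 95.9%.
- Highest (10%, 2%, 80%): (441 + 0.4)/452 = 97.7%.

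Over the same grid specificity is 39–50% and the net reduction in X-rays 11–15%.

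A wider and harsher set takes 500 imaged patients (245 of 250 fractures detected) and all non-imaged patients rule-negative. With 10% not imaged (56 patients) and 0, 2, 5 or 10% of them fractured, sensitivity is 98.0, 97.6, 96.9 or 95.9%. With 30% not imaged (214 patients) it is 98.0, 96.3, 94.0 or 90.3%. If no non-imaged patient has a fracture, sensitivity does not change.

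**What it could do to the model.** This was simulated with 400,000 patients and three binary predictors. When imaging depended only on the modelled predictors (81% imaged), the coefficients were essentially unchanged, while for a rule of any predictor positive:

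- sensitivity was 0.979 in imaged patients and 0.964 in all;
- specificity was 0.122 and 0.188;
- the area under the ROC curve (AUC) was 0.719 and 0.730.

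When imaging also depended on an unrecorded clinical impression (77% imaged), the intercept moved from −1.94 to −1.68 and the slopes shrank (1.33 to 1.23, 1.06 to 0.97, 0.70 to 0.65). Mean predicted risk over all patients was then 0.445, against 0.418 observed. These values depend on the simulated set-up; they show the mechanism, not this study's bias.

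**The case against.** The best case for the plan has five parts.

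- **The limitation is disclosed**, in the abstract and in the Discussion, and imaging everyone is said not to be feasible. This stands: nothing is concealed. The fault is that the limitation is dismissed by an argument that contradicts the stated population.
- **The unverified group may be small.** The abstract says that these patients are routinely referred for radiology, and Study procedures refers to national guidelines. This also stands, and it is why no size can be claimed. The illustration is in addition unfavourable in one respect: applying the 90% rule-negative share to non-imaged fractures gives the rule 10% sensitivity there, against 98% in imaged fractures. Even so, sensitivity falls by only 1.3 points.
- **The CRF group may be wider than the eligible group.** The Discussion speaks of wrist pain after injury, the inclusion criterion of pain on pressure. Some non-imaged patients may be ineligible, so the overlap is unknown. The contradiction remains for those who are eligible.
- **The named accuracy measures are goodness of fit and a ROC curve.** A ROC curve is made of sensitivity and specificity, so the point carries over, but X-rays saved is not a planned estimate.
- **An analysis of imaged patients is coherent.** It is, provided the population, aim and intended use say so. At present they do not.

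A reader might infer that the rule itself must be biased. The documents do not support that. If imaging depends only on modelled CRF items, a correctly specified model keeps its coefficients, and only its performance in the wider population differs. Nor is the direction always unfavourable: specificity and AUC may be better in the full population.

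**Conclusion.** The concern holds as a contradiction about the population, with a consequence for what the performance figures mean. Discrimination, accuracy and fracture prevalence will describe imaged patients and may differ in the population that Study population defines. The coefficients are affected as well only if imaging depends on clinical impression that the CRF does not record. The protocol's claim that the objection is disposed of is not supported.

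The size cannot be derived from the protocol. Under the moderate assumptions above, an apparent sensitivity of 98% becomes about 96–98%; the harsher set runs from no change to 90.3%. A reader might take these as estimates of the study's bias, but they are conditional on inputs that the protocol does not give.

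This should be fixed, because it decides to whom the rule may be applied. It does not invalidate the design, and consistent wording alone would be enough.

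**What to change.** Delete the Discussion sentence that declares objections answered. Then reconcile the abstract, the aims in Background, Study population, Inclusion criteria, Statistical analysis and Discussion in one of two ways.

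**(a) Limit the claim.** State throughout that the population, the aim and the rule concern only patients already selected for X-ray, and that the rule can therefore only identify X-rays to omit among them. Changing the abstract, Statistical analysis and Discussion alone would not do, because the aim and the population are set in Background, Study population and Inclusion criteria. Cost: wording, and a narrower claim.

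**(b) Keep the population as defined.** Report, per hospital, the number and CRF profile of eligible patients who were not imaged. Beside the imaged-only analysis, add a verification-corrected sensitivity analysis: inverse-probability weighting for being imaged, or multiple imputation of the outcome, from the CRF items. Show results over a range of fracture rates in the non-imaged group. Cost: analysis of CRF data that the Discussion says are collected anyway, wider standard errors, and possibly large weights for profiles that are rarely imaged. The correction assumes that imaging is explained by the CRF items. It cannot remove selection on unrecorded impression, which is why the range is needed.
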